### Causality definitions

An adverse event or reaction is considered **related** to the research intervention (i.e. radiotherapy) if there is a reasonable possibility that the reaction or event may have been caused by the research intervention (i.e. a causal relationship between the reaction and the research intervention cannot be ruled out by the investigator(s)).

The relationship of an AE to the study treatment (causality) will be described using the following definitions:
Unrelated: Any adverse event for which there is evidence that an alternative etiology exists or for which no timely relationship exists to the administration of the study treatment and the adverse event does not follow any previously documented pattern. The adverse event, after careful consideration by the investigator, is clearly and incontrovertibly due to causes other than the intervention.Unlikely: Any adverse event for which the time relationship between the study treatment and the event suggests that a causal relationship is unlikely and/or the event is more likely due to the subject’s clinical condition or other therapies concomitantly administered to the subject.Possible: Any adverse event occurring in a timely manner after the administration of the study treatment that follows a known pattern to the intervention and for which no other explanation is known. The adverse event, after careful consideration by the investigator, is considered to be unlikely related but cannot be ruled out with certainty.Probable: Any adverse event occurring in a timely manner after the administration of the study treatment that follows a known pattern to the intervention and for which no other explanation is known. The adverse event, after careful consideration by the investigator, is believed with a high degree of certainty to be related to the intervention.Definitely Related: Any adverse event occurring within a timely manner after administration of the study treatment that is a known sequela of the intervention and follows a previously documented pattern but for which no other explanation is known. The adverse event is believed by the investigator to be incontrovertibly related to the intervention.

### Severity

The severity of adverse events will be evaluated using the Common Terminology Criteria for Adverse Events (CTCAE) v4.0 grading scale [21].
Grade 1: MildGrade 2: ModerateGrade 3: SevereGrade 4: Life-threatening or disablingGrade 5: Death

Note: The term “severe” is a measure of intensity: thus a severe adverse event is not necessarily **serious**. For example, nausea of several hours’ duration may be rated as severe, but may not be clinically serious.

### Immediately reportable adverse events

Any grade 4 or 5 adverse reaction that is definitely, probably, or possibly the result of experimental treatment (i.e. radiotherapy) must be verbally reported to the Principal Investigator and Coordinating Centre within 24 h of discovery, and to the approving REB if necessary as per their reporting guidelines.

Local and non-local SAEs will be reported to the applicable REB as per their reporting guidelines. All **serious**, **unexpected** adverse events or reactions **regardless of causality** will be reported within **7** days of discovery to the pertinent REB, or as required as per the REB guidelines.

Note: conditions that are NOT related to protocol treatment or baseline Interstitial Lung Disease are not considered a SAE in this protocol.

## Subject withdrawal

Subjects may voluntarily discontinue participation in the study at any time. If a subject is removed from the study, the clinical and laboratory evaluations that would have been performed at the end of the study should be obtained. If a subject is removed because of an adverse event, they should remain under medical observation as long as deemed appropriate by the treating physician.

## Followup and assessment of efficacy

Patients will be seen in follow-up as per Table 5. At each visit, a history and physical examination will be conducted by the oncologist, and CTCAE toxicities recorded, and quality of life questionnaires will be completed.

**Table 5 Tab5:** Follow-up evaluations

	Before Treatment	Year 1^a^	Year 2–5^a^
History and Physical	X	3, 6, 9, 12 mo	18 mo, 24 mo, then annually
Assessment by Respirology/Pulmonology	X	At least every 6 months	At least annually
Central review of ILD diagnosis	X		
PET/CT	X		
Brain MRI	If symptoms (see Pre-treatment Evaluation)		
Mediastinal staging	Optional (see Pre-treatment Evaluation)		
HRCT chest	X	3, 6, 12 mo	18 mo, 24 mo, then annually
PFTs^b^	X	6, 12 mo	18 mo, 24 mo, then annually
Toxicity Scoring	X	3, 6, 9, 12 mo	18 mo, 24 mo, then annually
FACT-L, EQ-5D-5L QOL scoring and cough severity scale	X	3, 6, 9, 12 mo	18 mo, 24 mo, then annually

^a^All times are measured from end of radiation

^b^To avoid duplication of PFTs, if the patient is having PFTs done by other physicians (e.g. respirologists), the PFTs must only be +/− 2 months of the dates stated above to be acceptable

CT chest will be repeated at 3, 6, 12, 18 and 24 months, then annually. Additional imaging or laboratory investigations may be carried out at the discretion of the oncologist. Pulmonary function tests will be repeated at 6, 12, 18, and 24 months.

### Follow-up of patients declining study intervention

It is expected that some of patients who are offered participation in this trial decline the intervention, and thus would normally decline to enter the study. Patients who decline enrollment on the trial because they do not want to receive radiation will be asked to consent to follow-up phone calls (at 3-monthly intervals for 2 years) and prospective inclusion of their clinical data collected from the medical record as part of a cohort of patients declining radiotherapy. The phone calls will ask the participant about pulmonary symptoms (in the same manner as toxicity scoring is done in patients who receive radiotherapy), and any other cancer treatments received.

### Measurement of response

Survival outcomes: OS will be measured as time until death from any cause, and progression-free survival as time to either local, regional or distant progression or death, whichever occurs first.

### Disease response and progression

Assessment of response on imaging after SABR is difficult, as fibrotic changes in the lung may obscure tumor measurements. Nonetheless, the Response Evaluation Criteria in Solid Tumors (RECIST) 1.1 [23] will be used.

Response to SBRT will be assessed by a central review process, where the PI and at least one other member of the trial committee will review the diagnostic imaging prior to data analysis to determine response. Histological confirmation and/or PET scan may be recommended to assess cases suspicious for recurrence. Any lesions that exhibit growth as per RECIST 1.1 criteria will be counted as progression, unless subsequent scans show a period of no growth of > 6 months.

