### Secondary endpoints

CTC-AE 4.0 toxicity
Including risk of treatment-related mortality within 6 months of radiotherapy.Including an analysis of pulmonary toxicity stratified by anti-fibrotic drug useProgression-free survival: defined as time from enrollment to death from any cause or any progression of disease (local, regional or distant)Local controlChanges in cough severity (using a 10 cm visual analogue scale)Rates of acute-exacerbation of IPF (in IPF patients), defined using Collard 2016 criteria:
Acute worsening or development of dyspnea > 1 month durationComputed tomography (CT) with new bilateral ground-glass opacity and/or consolidation superimposed on a background pattern consistent with usual interstitial pneumonia patternDeterioration not fully explained by cardiac failure or fluid overloadRates of acute-exacerbation of ILD (in non-IPF patients), defined using the same Collard 2016 criteriaQuality of Life (Functional Assessment of Cancer Therapy – Lung (FACT-L) and EuroQol 5-Dimensional 5-Level (EQ-5D-5L))Changes in ILD severity as qualitatively measured on HRCT (i.e. HRCT fibrosis score and HRCT total disease score)Changes in pulmonary function tests, including diffusing capacity of the lungs for carbon monoxide (DLCO), forced expiratory volume in 1 s (FEV_1_), and forced vital capacity (FVC).Exploratory quantitative analysis of HRCT features (i.e. radiomics)Analysis of outcomes for patients who otherwise meet the study enrollment criteria but decline radiotherapy.

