### Exclusion criteria

Prior invasive malignancy except non-melanomatous skin cancer, unless the patient has been disease free for at least of 2 year.Prior thoracic radiotherapyPlans for the patient to receive other local therapy while on this study, except at disease progression;Plans for the patient to receive systemic therapy (standard chemotherapy, biologic targeted agents or immunotherapy) while on this study, except at disease progression. Patients are allowed to receive anti-fibrotic agents used in the treatment of IPF or non-IPF fibrotic ILD (e.g. nintedanib, pirfenidone), or steroids, if those are part of their current ILD treatment regimen. Other immunosuppressive drugs such as mycophenolate, azathioprine, cyclophosphamide, and rituximab must be stopped for 2 weeks prior and 2 weeks after treatment.Active pregnancyConcurrent administration of any drugs with known radiosensitive effects (e.g. Methotrexate).

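### The rule that cancels RECIST growth after more than 6 stable months does not exclude scans taken after new anticancer therapy, so a salvaged local failure can be recoded as no progression

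*Protocol article*

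**What the plan says.** All references are to the protocol article.

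- **Progression rule** (Disease response and progression): "Any lesions that exhibit growth as per RECIST 1.1 criteria will be counted as progression", followed at once by the exception "unless subsequent scans show a period of no growth of > 6 months".
- **Reason for caution** (same section): "fibrotic changes in the lung may obscure tumor measurements".
- **Confirmation** (same section): "Histological confirmation and/or PET scan may be recommended to assess cases suspicious for recurrence". This is optional, and the exception does not refer to it.
- **Review** (same section): the principal investigator and at least one further trial committee member assess the imaging before the data are analysed, so they can see scans taken after the growth.
- **Further treatment** (Exclusion criteria): planned systemic therapy is barred, including "biologic targeted agents or immunotherapy) while on this study, except at disease progression". Other local therapy is barred with the same exception.
- **Endpoints** (Secondary endpoints): PFS is "defined as time from enrollment to death from any cause or any progression of disease (local, regional or distant"), and local control is listed separately.
- **Imaging** (Followup and assessment of efficacy): "CT chest will be repeated at 3, 6, 12, 18 and 24 months, then annually".

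**The concern.** The exception has a sound purpose: fibrosis after radiotherapy can look like tumour growth, and a long stable period suggests that it was not tumour. That inference works only while the lesion is left untreated. Once new therapy has started, stability may mean that a real recurrence responded to it. The rule as written treats the two cases alike, although the same document foresees treatment at progression.

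A local failure controlled by a second treatment could then be credited to the study radiotherapy. Reversal is also open only to patients who survive and keep being scanned for more than 6 months after the growth, so whether an event counts depends partly on later survival. The trial has a single arm, so no concurrent group shares the distortion.

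**Working it through.** The plan states no figure for this rule, so there is nothing to reproduce. The check has two parts.

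**1. Does the rule, followed literally, remove a salvaged recurrence?**

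Take a patient whose treated lesion meets RECIST growth on the month 12 CT.

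- Step 1: the growth counts as progression under Disease response and progression.
- Step 2: the exclusion criteria now allow other local or systemic therapy.
- Step 3: the CTs at months 18, 24 and 36 show no growth. Counted from the growth scan, the stable time is 36 − 12 = 24 months. Counted from the first stable scan, it is 36 − 18 = 18 months. Both exceed 6 months.
- Step 4: the exception is met, because it has no condition on treatment or on histological confirmation. The local failure disappears, and PFS runs on to a later progression, death or censoring.

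After month 24 the CT interval is 12 months, so one stable interval is then enough. A patient who dies or stops imaging within 6 months of the growth can never meet the exception.

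**2. How large could it be for local control?**

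Inputs:

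- n = 39 (required sample size, Methods/design).
- Local control of about 90% at 3 years after this type of radiotherapy in general (Background). It is not specific to interstitial lung disease. Local failure is then about 10%.
- Share of local failures that are treated and then stable for more than 6 months: not in the document. Assumed 20-40%.

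Formula: recoded patients = n × P(local failure) × P(durably salvaged | local failure).

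- Local failures: 39 × 0.10 = 3.9, about 4.
- Lower end: 3.9 × 0.20 = 0.78 patients; 0.78 / 39 = 2 percentage points.
- Upper end: 3.9 × 0.40 = 1.56 patients; 1.56 / 39 = 4 percentage points.

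A wider assumed range, with 25-75% of failures salvaged and 30-70% of those stable for more than 6 months, gives:

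- Low: 0.10 × 0.25 × 0.30 = 0.0075, or 0.75 points; 39 × 0.0075 = 0.29 patients.
- High: 0.10 × 0.75 × 0.70 = 0.0525, or 5.25 points; 39 × 0.0525 = 2.05 patients.

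These are crude proportions. For PFS the effect of recoding at the treated site is smaller, because a later progression or death remains an event and many reversals would only delay the event date.

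**The case against.** **The words are an inference.** The document nowhere says that growth is cancelled even after new treatment. The rule is aimed at fibrosis, at least two reviewers read the scans, and histology or PET can be recommended. Sensible reviewers might keep a recurrence that they knew had been treated. This stands as a limit: the claim concerns what the text permits. But nothing in the text tells the reviewers to keep the event.

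**It is a detail for the analysis plan.** Handling of later therapy often is left there. Here, however, the article states an operative rule, and its section on radiation therapy adverse events sends investigators to this same passage for the criteria of progressive disease. The point is about a stated rule that gives a wrong result when followed.

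**Regional and distant progression.** A reader might infer that the exception also erases regional and distant failures, since PFS counts all three. The documents do not support that as a general statement. The exception applies to lesions that grow, whereas patients enter as N0 M0, so regional or distant failure would mostly appear as new disease. Enlarged nodes with a negative biopsy at entry are a narrow exception.

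**A larger bias.** A reader might infer an overstatement of 5-15 points by assuming 10-15 progressions in 39 patients, with 20-40% of them reversed. No progression or salvage rate in the document supports this. It exceeds what the general local control figure implies, and it treats every reversed patient as event-free in PFS. Durable salvage may also be uncommon in patients with fibrotic lung disease who are unfit for surgery or have declined it.

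**Direction.** A patient with fibrotic pseudo-growth who dies or stops scanning within 6 months keeps a false progression, which works downward. This stands. The upward statement applies to salvaged recurrences, and the net effect of survival-dependent reversal is not fixed.

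**Consequences.** No decision rule uses local control or PFS. This stands and sets the severity.

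**Conclusion.** The concern holds in a limited form. As written, the exception allows a true recurrence, chiefly at the treated site, to be recoded as no progression after successful salvage. This overstates local control and, to a lesser extent, PFS. Reversal is also available only to patients who live and continue imaging.

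The document does not fix the size. About 1-2 of 39 patients, or 2-4 percentage points of local control, follows from two assumptions: that the general figure of about 90% applies to this population, and that 20-40% of local failures are durably salvaged. Under the wider salvage range the effect could be below 1 point.

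The primary endpoint (overall survival), the criteria for judging the treatment worthwhile (survival, grade 3 or 4 pulmonary toxicity, treatment-related mortality) and the de-escalation rule (grade 5 toxicity) do not depend on this sentence. Severity: minor.

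**What to change.** Amend the sentence in Disease response and progression so that growth meeting RECIST 1.1 may be reclassified only if all of these hold:

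- the growth lies in or next to the irradiated volume;
- recurrence has not been confirmed histologically;
- the more than 6 months without growth are shown on scans taken before any new anticancer therapy.

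In every other case the event stays, dated at the first scan that shows growth.

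Report local control and PFS without any reversal as a sensitivity analysis.

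The cost is one sentence, a check of therapy start dates against scan dates at central review, and one extra analysis run. The protection against fibrosis is kept in the main analysis. In the sensitivity analysis some fibrosis will count as progression, so its estimates should be read as the pessimistic end.

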## Statistical considerations

### Statistical design and sample size

The primary endpoint of this study is overall survival in patients able to be treated with a dose of 50 Gy in 5 fractions, with a comparison to historical controls of untreated medically inoperable patients stage I NSCLC, which consistently have survivals of less than 1 year, as described in the Background section. Demonstration in this study that median OS after SABR is statistically greater than a historical control of < 12 months would indicate that SABR is worthwhile in this population of ILD patients, if toxicity is within acceptable limits.

A sample size of 39 patients provides >80% power to detect an OS improvement of >20% at 1 year, compared to a historical control of <50% (i.e. 70% vs. 49%), using a one-sample, one sided binomial test at the 0.05 significance level, assuming 10% dropout or loss to follow-up before one year. All cohorts will be combined for this primary analysis.

SABR will be considered worthwhile if OS is > 1 year, the risk of grade 3 or 4 pulmonary toxicity is < 35%, and the risk of treatment-related mortality is < 15%.

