### Rationale for a study

For patients with ILD and concurrent early-stage lung cancer who are not candidates for surgery, these data showing high rates of toxicity have led to a difficult clinical dilemma, since there are few alternate treatment options. The option of delivering no treatment whatsoever, which avoids any risk of treatment-related toxicity, is associated with a high risk of death due to the lung cancer itself. The median survival for untreated stage I NSCLC is only 6–8 months, with 1-year mortality of 60–70% [12], much higher than the risks associated with SABR treatment. For example, in one study of untreated patients with NSCLC in the U.S. National Cancer Database, the median survival for patients with stage I NSCLC who were unfit for an operation was 7.6 months [13]. This suggests that even in patients with an ILD-GAP score > 5, the risk of death due to lung cancer within 1 year exceeds the risk of death due to ILD or complications of SABR.

As a result, patients with ILD and early-stage NSCLC are often advised, after discussion of their case at a multidisciplinary conference, that treatment with SABR provides the best chance of local control and cure, but that SABR is associated with an appreciable risk of treatment-related toxicity. For patients undergoing SABR under this scenario, the optimal dose and fractionation is unknown.

It is possible that currently-used doses and fractionations of SABR, when given with strict planning criteria to minimize the risk of lung toxicity, have only a modest risk of treatment-related toxicity and represent the best possible approach.

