### Rationale for primary endpoint and study design

Important outcomes for patients with NSCLC and ILD include both toxicity and oncologic outcomes, and both were considered as possible primary endpoints.

Pulmonary toxicity was not chosen as a primary endpoint because it is very difficult to distinguish between radiation pneumonitis and ILD exacerbations. The patients included herein are expected to develop ILD exacerbations as part of the natural history of their ILD, and they are at risk of ILD-related death, which is difficult to distinguish from pneumonitis-related death. Erroneous attribution of ILD exacerbations to radiation could lead to the incorrect conclusion that the radiation dose should be lowered. In essence, the subjectivity of assigning the cause of toxicity should not be part of the primary outcome due to the risk of misattribution. However, pulmonary toxicity outcomes will be closely monitored in this trial.

Overall survival (OS) was chosen as the primary outcome as it objectively reflects the potential benefits of treatment (i.e. extended survival), the harms of treatment (grade 5 toxicity), and the natural history of the ILD disease process itself. Since the median survival of untreated Stage I NSCLC in inoperable patients is consistently reported as < 1 year (as noted above), we hypothesize that the use of SABR can achieve a median OS of > 1 year in patients with ILD. Though pulmonary toxicity is not to be the primary outcome in this trial, it will nevertheless be closely monitored to determine whether subsequently-enrolled patients will receive a deescalated radiation regimen.

SABR will be considered worthwhile if median OS is > 1 year with an acceptable risk of toxicity, defined as a grade 3 or 4 pulmonary toxicity rate of less than 35% and a risk of treatment-related death of less than 15%.

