## Patient selection

### Inclusion criteria

Stage T1–2, N0, M0 (American Joint Committee on Cancer (AJCC) Staging, 8th Edition – i.e. tumor size ≤5 cm) prior to registration.Not a candidate for surgical resection, determined by any of the following:
Consultation with a thoracic surgeonDiscussion at multidisciplinary tumour conference with a surgeon presentPatient refusal of surgeryPathologically (histologically or cytologically) proven diagnosis of non-small cell lung cancer (NSCLC) is not required, but strongly recommended.
If the risk of biopsy is unacceptable, pathologic confirmation is not required providing there is growth over time on CT imaging and/or fluorodeoxyglucose (FDG) avidity that is strongly suggestive of a primary NSCLC.Eastern Cooperative Oncology Group (ECOG) performance status 0–3.Age ≥ 18.Life expectancy > 6 months.Fibrotic interstitial lung disease of any subtype, as diagnosed by a respirologist/pulmonologist and confirmed by central review.

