### Procedure if lung constraints cannot be met

**The lung constraints are critically important for this study.** If one or more of the lung constraints cannot be met, even after varying the prescription isodose surface percentage between 60 and 90%, PTV coverage must then be compromised. Target coverage may be reduced until 95% of the IGTV is receiving the 95% of the prescription dose, and 90% of the IGTV is receiving 99% of the prescription dose, with the PTV covered as well as possible while respecting lung constraints.

**If the lung dose constraints still cannot be met, the patient should be treated with a 10 or 15-fraction regimen.** Such patients treated with protracted regimens due to inability to meet dose constraints will not count toward the primary analysis, but should still be followed for toxicity and outcomes. Such patients will be reported as a separate cohort.

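### The 1-year survival test uses medically inoperable controls, but patients who enter only because they refuse surgery count fully, and no stated analysis separates them

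*Protocol article*

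**What the plan says.** **The benchmark.** Statistical design and sample size sets the primary comparison "with a comparison to historical controls of untreated medically inoperable patients stage I NSCLC" and puts figures on it, "compared to a historical control of <50% (i.e. 70% vs. 49" percent. Rationale for primary endpoint and study design rests the hypothesis on the same group: "Since the median survival of untreated Stage I NSCLC in inoperable patients is consistently reported as < 1 year". The one study described individually, in Rationale for a study, gives a median for "patients with stage I NSCLC who were unfit for an operation was 7.6 months".

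**Who enters.** The Inclusion criteria read "Not a candidate for surgical resection, determined by any of the following", followed by three routes: a thoracic surgeon's consultation, a tumour conference with a surgeon present, or the patient's refusal of surgery. Any one is enough, so refusal without medical unfitness qualifies.

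**Who is analysed.** "The primary endpoint of this study is overall survival in patients able to be treated with a dose of 50 Gy in 5 fractions", and "All cohorts will be combined for this primary analysis". The stated exclusions concern dose or fractionation. Under Procedure if lung constraints cannot be met: "Such patients treated with protracted regimens due to inability to meet dose constraints will not count toward the primary analysis". Under Data safety monitoring, patients on de-escalated doses do not count towards accrual. The stated splits are by ILD severity (Fig. 1), anti-fibrotic use for pulmonary toxicity (Secondary endpoints) and dose level (Data safety monitoring). None is by route of entry.

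**How the population is described.** The Discussion calls it medically inoperable, which is narrower than the Inclusion criteria.

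**The concern.** In a single-arm trial the benchmark is the control arm, so it should describe the patients set against it. Someone fit for an operation who declines it may have fewer competing causes of death than someone judged unfit. If so, part of any survival above 49% reflects who was enrolled rather than what SABR did, and the test cannot tell the two apart.

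At stake is the efficacy half of the trial's conclusion, namely that SABR beats no treatment in medically inoperable patients with ILD. This is more than a detail that a SAP would normally settle. The article itself fixes the comparator, the entry rule and the pooling, and they do not describe the same patients. A later SAP can separate refusers only if the route of entry was recorded.

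**Working it through.** **Inputs from the Protocol article (Statistical design and sample size).** Null p0 = 0.49, alternative p1 = 0.70, one-sided one-sample binomial test at 0.05, N = 39, 10% dropout. Rationale for a study gives 1-year mortality of 60–70% in untreated stage I disease, that is, 1-year survival of 30–40%.

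**Assumed, because the article gives neither.** The number of refusers m among the evaluable patients, and their 1-year survival.

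**1. The plan's own figure.** n = [(1.645·√(0.49·0.51) + 0.842·√(0.70·0.30)) / 0.21]² = 33.1, so 34 evaluable; 34 / 0.90 = 37.8, so 38 enrolled, against the stated 39. Exact test:

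| Evaluable | Reject at | True error | Power at 70% |
|---|---|---|---|
| 34 | 22 or more alive | 4.8% | 80.7% |
| 35 | 23 or more alive | 3.5% | 77.3% |
| 39 | 25 or more alive | 4.2% | 83.6% |

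The stated size and power are essentially reproduced (the dip at 35 is the sawtooth of the exact test). The issue is comparability, not the sample-size arithmetic. From here n = 35, since 39 × 0.90 = 35.1.

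**2. Effect of refusers.** Let the other 35 − m patients survive 1 year with probability b and the m refusers with probability r. Then P(reject) = P(X + Y ≥ 23), with X ~ Bin(35 − m, b) and Y ~ Bin(m, r) independent. For m = 7 (20%):

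| Refusers' 1-year OS | b = 49% | b = 40% | b = 30% |
|---|---|---|---|
| 40% | 2.1% | 0.2% | <0.1% |
| 50% | 3.7% | 0.4% | <0.1% |
| 60% | 5.9% | 0.7% | <0.1% |
| 70% | 9.0% | 1.3% | <0.1% |
| 80% | 13.2% | 2.1% | 0.1% |
| 90% | 18.5% | 3.3% | 0.15% |

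**3. Other shares, refusers at 80–90%.** With b = 49%: 7.7–9.6% for m = 4 and 21–32% for m = 10. With b = 40%: 5.1–9.1% for m = 10 and 14–28% for m = 14. With b = 30%: 2.6–6.6% even for m = 14.

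**4. Margin in the null.** The mixture reaches 49% when the refuser share is (0.49 − b)/(r − b). For r = 0.80 that is 0.09/0.40 = 22.5% at b = 0.40 and 0.19/0.50 = 38% at b = 0.30.

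**5. Cost of testing again without refusers.** With 28 patients the exact test rejects at 19 or more alive, with power 68% at 70%, against 77% with 35. Requiring both tests to reject gives about 66%. For an estimate, the approximate 95% half-width at 70% is 1.96·√(0.21/28) = 17.0 points, against 1.96·√(0.21/35) = 15.2 points.

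**The case against.** **The high refuser survival is unsupported.** If SABR adds nothing, a refuser is in effect an untreated stage I patient. Rationale for a study gives its 6–8 month median and 60–70% 1-year mortality for untreated stage I disease without limiting them to inoperable patients; only the individual study is so limited. At 40% survival refusers lower the rejection rate. This stands: 80–90% cannot be the headline, which is why the table runs down to 40%. It does not remove the mismatch, since two other sections label the benchmark inoperable.

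**The null already has a margin.** At 49% it lies 9–19 points above the survival implied by the Background. This stands: at that survival, 7 refusers never bring the rejection rate above 3.3%.

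**Other differences run the opposite way.** Every trial patient has fibrotic ILD, which the cited controls are not said to have, and ILD severity gives 3-year mortality of 10% to 75%. Stage IIA is admitted, while the benchmark is stage I. Refusers with ILD need not be fit. All of this stands. It means that the net direction is unknown; it does not mean that the differences cancel.

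**The plan has related provisions.** Eligible patients who decline radiotherapy are followed as a separate cohort, which gives useful context but does not enter the primary test. Calling SABR worthwhile also needs grade 3–4 pulmonary toxicity below 35% and treatment-related mortality below 15%.

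**Sensitivity analyses and form fields often sit in a SAP or full protocol.** True, and their absence here is not the defect. The defect is that the article's comparator and its entry rule disagree.

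**Conclusion.** The mismatch holds on the text: the benchmark and the Discussion concern medically inoperable patients, the entry rule is wider, and patients admitted by refusal alone count fully. The comparison can therefore be biased upward.

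Its size is conditional. With 7 refusers among 35 and refuser survival of 50–90%, rejection is about 4–19% if the remaining patients sit exactly at 49%, and at most 3.3% if they sit at 30–40%. The share of refusers and their survival are assumptions throughout.

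Three stronger readings are tempting and are not supported:
- That the design has a false-positive rate of 13–32%. This needs 80–90% survival in 20–30% of patients together with a 49% base in the rest.
- That the trial is biased upward on balance. ILD and stage IIA work against that, and the article gives nothing with which to weigh them.
- That these are chances of wrongly declaring SABR worthwhile. That declaration also depends on the two toxicity limits.

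The correction is cheap and worth making for comparability and interpretation. The sample size and the primary test can stay as they are.

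**What to change.** 1. Record at registration which route established that the patient was not a surgical candidate: surgeon's consultation, tumour conference, or refusal only.
2. Add to Statistical design and sample size, for example: *As a supportive analysis, 1-year overall survival with its confidence interval will be estimated without patients eligible only by refusal of surgery and set against 49%. Refusal-only patients will be reported separately. The conclusion about medically inoperable patients will be interpreted in light of this estimate.*
3. Align the population described in the Inclusion criteria, Statistical design and sample size, and the Discussion, so that it is clear whom the conclusion covers.

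The conclusion should not depend on a second significant test. With 28 patients that test has 68% power, and requiring both tests gives about 66%, against 77% for the primary test at 35.

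**Cost.** One registration field, one extra estimate and no extra patients. The downside is a wider interval in the restricted set, about ±17 rather than ±15 points with 7 refusers. Limiting the primary set to inoperable patients and still wanting 39 of them would cost far more: 39/0.9, 39/0.8 or 39/0.7, that is, 44, 49 or 56 patients for 10%, 20% or 30% refusers.
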